## Abstract

Human papillomavirus (HPV) is a common sexually transmitted infection that can lead to HPV-related cancers such as cervical cancer and other cancers such as anal, vaginal, and penile cancer. HPV rarely produces symptoms and cannot be cured or treated; therefore, vaccination is essential to protect against HPV and HPV-related diseases. However, young Aboriginal and Torres Strait Islander (hereafter, respectfully, ‘Aboriginal’) people are not receiving their HPV vaccine dose, resulting in missed opportunities to be protected from HPV-related cancers.

Health promotion is a critical way to empower people to take ownership over and control their health and is a core function of public health. One way to deliver health promotion is through social media platforms. In recent COVID-19 times, we have seen the effect of social media on public health messaging, both positive and harmful. In particular, Instagram influencers have had a profound impact on pro- and anti-vaccination messages. Aboriginal adolescents aged 13-15 years old have strong engagement with social media platforms. Combining co-created health promotion messages with local ‘micro-Influencers’ is a novel way to improve HPV vaccination rates.

The overall aim of this project is to improve the rates of HPV vaccination amongst young Aboriginal people. We will achieve this through: i) co-creation of health promotion messages, ii) developing and delivering a social media campaign and iii) evaluating the effectiveness of the campaign through an interrupted time-series design. We hypothesise that the co-creation of health promotion messages with young Aboriginal people and their families and utilising the skills of micro-Influencers to engage and influence their followers will result in improvements HPV vaccination rates amongst this population.

## Introduction

Human papillomavirus (HPV) is a common sexually transmitted infection that can lead to HPV-related cancers such as cervical cancer and other cancers such as anal, vaginal, and penile cancer.
^
1,
2
^ HPV rarely produces symptoms and cannot be cured or treated; therefore, vaccination is essential to protect against HPV and HPV-related diseases.

In 2007, Australia initiated the HPV vaccine through the National Immunisation Program (NIP) to girls aged 12 to 13 years in 2007 and to boys in 2013; catch up programs were implemented for older age groups. Up until 2023, the HPV vaccine provided as a free two-dose program for both males and females aged 12-13 years, with doses given between 5-6 months apart through school-based programs.
^
3
^ Responding to the global decline in HPV vaccination, lack of access to the vaccine and cost and burden required for two doses, WHO released updated recommendations in 2022 that a single dose was effective in reducing HPV.
^
4
^ As of 2023, Australia has transitioned to the single dose for 12-13 year olds through the NIP delivered at school with young people up to 26 years old also eligible for the free HPV vaccine. If a vaccine dose is missed at school, depending on their place of residence, a young person may receive a free catch-up dose at their school, their local Aboriginal or government health centre, or private general practitioner.

### Immunisation program impacts

In Australia, the prevalence of the HPV types in women aged 18 to 24 years old which were targeted by the vaccine declined significantly from 28.7% in the pre-vaccination era (2005-2007), to 2.3% in vaccinated women after vaccine introduction (2010-2012).
^
5
^ The rate of high-grade cervical disease has also declined dramatically, by 2014 it dropped to less than half the 2007 rate in women under 20 years of age.
^
5
^ The introduction of the Gardasil 9 vaccine is expected to prevent up to 90% of cervical cancers. Some research suggests that increased HPV vaccination, together with greater participation in screening, has the potential to eliminate cervical cancer in Australia and elsewhere within a few decades.
^
5,
6
^

In Australia, young Aboriginal and Torres Strait Islander (hereafter, respectfully, Aboriginal) people do not receive their HPV vaccine dose, resulting in missed opportunities to be protected from HPV-related cancers.
^
4
^ This is particularly important as rates of cervical cancer in Aboriginal women are twice those of non-Indigenous women, mortality rates more than three times higher, and screening participation rates lower.
^
6–
9
^ The recent change to one HPV dose will have substantive impact on meeting the recommended dose proposed by WHO.
^
4
^ In 2022, the Australian national rate of having at least one dose of HPV vaccination for young people turning 15 years old was 83.0% for Aboriginal females and 78.1% for Aboriginal males.
^
10
^ In Western Australia (WA), the completion rates were 81.4% of Aboriginal females and 78.6% of Aboriginal males. Despite these overall rates being reasonable, there are pockets of concern within Western Australian, including the capital of the State, Perth. In 2022, 51% of Aboriginal young people in Perth received one dose of HPV vaccine during Year 7 and this did not improve in 2023 (unpublished data).
^
11
^ Substantive resources are needed to improve these rates both in school catch-up programs and within the community. To eliminate cervical cancer, improving HPV vaccine rates amongst young Aboriginal people is necessary.

Despite the decline in HPV, there are a number of reported barriers associated with HPV vaccine uptake including adolescents’ lack of awareness and knowledge, not feeling informed, and parental concerns around sexual activity and vaccine safety.
^
12
^ Adolescent boys were a ‘neglected’ group in understanding their barriers, with few studies examining the awareness, knowledge and intention of parents to vaccinate their boys.
^
12
^ COVID-19 has also had an impact on HPV vaccination with a global decline in HPV vaccination rates, particularly for low and middle income countries.
^
13
^ There is limited information on barriers and enablers regarding uptake of the HPV vaccine amongst global Indigenous communities.
^
14,
15
^ Acceptance of the vaccine included the provision of health information and school vaccination programs. In contrast, the lack of culturally appropriate information and services was identified as driving hesitancy. The intergenerational disruptions to communities and cultural traditions resulting from colonisation, and distrust of health systems due to histories of disadvantage and exploitation, are described as significant barriers.
^
14
^ While generalisability is limited, findings from this review echo those from Australian studies.
^
6,
16,
17
^

### Potential solution

For many young people, ‘[d] igital technology is regarded as an extension of self and social media is a primary mode of communication and social engagement’.
^
18
^ This extends to an interest in using social media for health-related information.
^
18,
19
^ A qualitative UK study with 13-18 year-olds found that the relatability and perceived sincerity of YouTube Influencers impacted their acceptance of health messages. Familiarity with the Influencer was also a factor for some younger males. At the same time, other participants were concerned that generalising an Influencer’s personal experiences carried a risk of negative effects.
^
20
^ Further research has found that tailoring strategies to the target culture, collaborating with community Influencers and ‘trusted messengers’, and leveraging ‘narratives and storytelling’ on various forms of social media to address specific health issues are likely to provide messages with greater reach and persuasive power.
^
19,
21
^ For young people, there is an increasing body of literature on social media use which cover issues such as substance use,
^
22
^ flu vaccination,
^
23
^ and sexual health
^
24
^ including HPV. Interventions in the general population for HPV vaccination using vehicles such as Facebook, YouTube, Twitter, Instagram
^
25–
27
^ and TikTok
^
28
^ have been found useful for enhancing issue awareness and providing information and autonomy in accessing and utilising, and in debunking misinformation.

Aboriginal people are high adopters of using social media platforms. Although data is limited on the use of social media platforms amongst young Aboriginal people, a 2014 survey of 400 Aboriginal participants of all ages found that 60% used Facebook compared to 42% of the Australian population.
^
29
^ The rise of TikTok has also had a big impact on Aboriginal creators and has fostered a community for young people to talk about their culture.
^
30
^ There are currently 42.1M posts of short videos related to or delivered by Australian Aboriginal people on TikTok (
https://www.tiktok.com/discover/australia-aboriginals
). Currently, it is the digital place to be for young people, having previously overtaken Snapchat, and is expected to become more popular than X (formally known as Twitter).
^
31
^ TikTok is the ideal place for a health promotion social media campaign for young Aboriginal people.

Social media Influencer posts are recognised in the literature as a potentially effective way to connect with young people and provide them with evidence-based health-related information. We have been unable to locate a social media campaign led by social media Influencers targeting Aboriginal young people with messaging encouraging them to get their HPV vaccine. Most campaigns that have targeted adolescents are highly scripted, traditionally come from established government or not for profit organisations, do not provide culturally relevant messages and/or are not co-created with young people. They also lack the capacity for young people to engage in the campaign and produce peer-to-peer sharing of information. Campaigns do not appear to consider cultural and other barriers to discussing STIs, sexual health, and the HPV vaccine, which is important when choosing messaging. In addition, utilising the skills of Influencers to engage their followers is likely to improve the acceptance of messages by their target audience.

Therefore, the
**overall aim** of this project is to improve the rates of HPV vaccination amongst young Aboriginal people. This will be achieved through the following aims:

*Aim 1:* Co-create health promotion messages with young Aboriginal people and their families.

*Aim 2:* Develop and deliver a social media campaign focused on these messages through micro-Influencers.

*Aim 3:* Evaluate the effectiveness of the campaign through an interrupted time-series design.

We
**hypothesise** that the co-creation of health promotion messages with young Aboriginal people and their families and utilising the skills of local micro-Influencers to engage and influence their followers, will improve HPV vaccination rates amongst this population.

## Protocol

### Setting and target population

This public health project will be delivered to male and female young Aboriginal people in the capital city of Western Australia (Australia), Perth. We have concentrated this project in Perth as i) it is not feasible to co-create effective health promotion messages for all regions of Western Australia due to geographic size (2.646 million km
^2^), and ii) given the large population of young Aboriginal people in the metropolitan area, we are able to effectively evaluate the impact of this project. Our primary target population will be young Aboriginal people aged 12-16 years old. The minimum age of involvement in the study is defined by the age that young people receive the vaccine at school and our maximum age is based on one-year post the age that is used for international reporting of HPV vaccination completion (see primary outcome). In 2023, we estimated 4983 young Aboriginal people aged 12-16 years old living in Perth.
^
32
^

### Collaboration

The project is a collaboration between Edith Cowan University (ECU), and the Aboriginal Health Council of Western Australia (AHCWA). Within AHCWA, the Public Health, Sexual Health and Blood Borne Virus, and Aboriginal Youth Programs will be actively involved in the project. The project will support two Aboriginal young people as ‘health promotion research assistants’ and be supported to formally develop their skills in health promotion.

### Cultural governance group

Given sensitivities surrounding this topic, we will have a Cultural Governance Group that will provide high-level cultural governance. The group will be comprised of the Aboriginal CIs ([name]), the Aboriginal health promotion research assistants, at least one young Aboriginal person aged between 13-15 years old, a family member who has a teenager, an Aboriginal community member and an Elder. The group will provide cultural advice to the social media team on the content and brief for the Influencers, branding and advice and coaching of Influencers.

They will also provide advice to the project team on question development and engagement of young people and interpretation of results.
Figure 1 provides the relationship between the Cultural Governance Group and the project and social media team. The group will meet quarterly in the first year and then biannually in years 2-4.

**Figure 1. f1:**
[figure not shown]
Relationship of cultural governance group to the project and social media team.

### Study design

This project will be delivered in three stages: (i) develop health promotion messages, (ii) develop and deliver a social media campaign, and (iii) evaluate the campaign using an interrupted time-series design.
Figure 2 provides an overview of the project including development of the campaign, qualitative and quantitative data collection and evaluation. We will use a controlled interrupted time series (CITS) design to determine the effectiveness of the social media campaign on HPV vaccination rates.

**Figure 2. f2:**
[figure not shown]
Interrupted time series design for identifying strength-based approaches that are feasible, sustainable and culturally safe for public health initiatives with Aboriginal and Torres Strait Islander peoples.

### Stage 1: Develop health promotion messages

*Aim 1: Develop health promotion messages through co-creation with young Aboriginal people and their families*

**Participants and recruitment**

To ensure messages are appropriately targeted to Aboriginal youth, we will invite young people aged 12-16 years old and their families for interviews. For young people, the aim will be to determine their understanding of the HPV vaccine and what messages would influence their uptake of the vaccine. We will also ascertain what Influencers they follow. Families will be encouraged to participate in the interviews as well. Families will be asked about their thoughts and understanding of the HPV vaccine and aspects that have previously (or would in the future) give them the confidence to support their children to receive the vaccine. We will take a multi-pronged approach to engaging young people and their families. We will engage families who have teenagers of this age through social media posts, community centres, and snowballing techniques. Family members and young people will be interviewed separately. Young people aged 12-13 years old will require family consent to participate in the study. Young people aged 14-16 can either consent for themselves or have the parent/guardian consent for them. If they wish to consent for themselves the Gillick Competency Screen will be completed to ensure they meet the criteria for a mature minor.
^
33
^ The two Aboriginal health promotion research assistants will be instrumental in recruiting young people and their families. We will recruit from 10 high school catchment zones with a high proportion of Aboriginal students attending schools. We will recruit ten young people aged 12-16 years and five families per catchment area to the project, totalling 100 12–16 year-olds and 50 families. Each person interviewed will be provided with a $50 voucher.

**Data collection and analysis**

We will offer individual face-to-face interviews and focus groups. Interviews will be completed by an experienced Aboriginal qualitative researcher who will also take a mentoring role with the health promotion research assistants to undertake interviews. Interviews will be recorded and transcribed. All qualitative information will then be synthesised descriptively, key messages will be identified, with thematic analysis completed using Nvivo software. Messages will also be discussed with AHCWA’s Sexual Health and Blood Borne Virus team and key stakeholders such as members of WA Health to review the messages for accuracy. At the end of this process, a list of facts and messages will have been developed, which will be discussed with the Cultural Governance Group and then utilised in ‘stage 2’ of the project. In addition, we will have developed a list of Influencers to approach.

### Stage 2: Develop and implement a social media campaign

*Aim 2a: Develop social media campaign through micro-Influencers
*

We have engaged social media campaign experts from DeeBlanche (
https://www.deeblanche.com/). They are a boutique marketing agency that specialises in developing and rolling out campaign brands for fashion and hospitality, and who have a unique understanding of the social media habits of Generation Z. The team will include experts in strategy development, production, execution, monitoring, reporting and evaluation of the campaign, and will be responsible for:
•
**Pre-strategy
**: Supporting question development and idea generation of brand.•
**Strategy development:** Understanding information from stage 1, key message development, branding, tone of the campaign, the timing of posts, content and brief for Influencers, and resource management.•
**Strategy implementation:** The roll-out of the campaign, support and recruitment of Influencers, scheduling of Influencer content, account management, reporting of activity/success, campaign reporting, and advice/coaching to Influencers.

Based on the advice from DeeBlanche, we will use TikTok as our platform for young people and Instagram and Facebook for families. For young people, we will engage at least five Aboriginal TikTok ‘micro-Influencers’ who have been identified in stage 1. Micro-Influencers are defined as Influencers who have up to 10,000 followers, have high engagement rates, strong relationships with their followers, and their opinions and perceptions are highly valued amongst their followers. Based on the experience of our social media team, micro-Influencers are the most appropriate type of Influencers to deliver this campaign compared to other types of Influencers (e.g. mega- and macro-Influencers). With the support of our social media team, micro-Influencers will provide content in their style. We will prioritise Aboriginal micro-Influencers, and they will be paid based on their industry rates, and own their own content. They will be required to add in #sponsored or equivalent to their posts. Influencers will not be expected to respond to comments on their posts, however, posts will be monitored by the social media team to provide feedback and mitigate any negative publicity or misinformation. During this stage, we will also develop linktrees that will be used as part of the campaign and will direct young people to relevant health services for catch-up HPV vaccination. For families, we will deliver content targeted to them via Instagram and Facebook as this platform has more engagement with this slightly older demographic. The Instagram and Facebook content will be general advertisement information developed by our social media team based on interviews in stage 1.

*Aim 2b: Implement a social media campaign*

We will deliver the campaign in Year 2 of the project (
Figure 3). The campaign will start prior to school term 1 and continue on to term 3. The timing of the campaign is to coincide with the school vaccination program, including parent consent and HPV dose 1 and the HPV vaccine catch-up program.
Figure 2 provides a social media campaign journey and focuses on the ‘engage ➔ excite ➔ convert’ part of the digital marketing strategy.
**‘Engage’** is priming young people about the social campaign for HPV. This will include the release of our campaign brand and launch of the website (weeks 1-6).
**‘Excite’** is the main part of delivering the campaign through micro-Influencers. Micro-Influencers will deliver up to 10 posts per week in total on their social media accounts during the build-up period (weeks 6-8), with 20-40 posts per week in total during the peak times (weeks 8-12). We expect this period to include organic content created by young people who are followers of the micro-Influencers and circulated through TikTok.
**‘Convert’** will be when young people have access to vaccinations (after week 12). During this period, we expect there will again be peer to peer posts created on TikTok that will keep the campaign’s momentum until the campaign starts again in term 3. Families will be targeted during weeks 2-3 and after week 12 through a content on Instagram.

**Figure 3. f3:**
[figure not shown]
Implementation of campaign during Term 1 and 3.

### Stage 3: Evaluation of the campaign

*Aim 3: Evaluate the effectiveness of the campaign through an interrupted time-series design*

**Controlled interrupted time series (CITS)**

This CITS study will be conducted over 72 months and includes three distinct periods: a 49-month pre-intervention period (2020-2023), a 4-month intervention period and a 19-month post-intervention period (2024-2025). ITS is a quasi-experimental design for assessing public health interventions and is a robust method when other designs such as randomised controlled trials are impractical. ITS study designs allow adjustment of potential biases such as secular trends, seasonal trends, random fluctuations, and autocorrelation compared to other quasi-experimental designs such as controlled before and after studies.
^
34
^ Inclusion of a control group can strengthen an ITS evaluation by allowing assessment of whether any observed impact of the intervention is likely causal, or could instead be due to co-interventions or other events occurring concurrently with the intervention.

**Intervention and control populations**

The social media campaign will be targeted to Aboriginal young people in the Perth region. The control group will be non-Aboriginal young people in the same location. We have chosen this characteristic-based control group because we expect that any co-interventions or concurrent events would likely affect both groups.
^
35
^ Therefore, if an impact is observed in both groups, this suggests it may be due to a co-intervention/concurrent event, while if the impact is only observed in the intervention series, this suggests the effect is more likely to be due to the intervention. During the intervention delivery we will collect information on events and interventions that occurred within Perth to improve HPV vaccination rates and who were the target population. We will report these in our final publication.

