•Level change at the end of the social media campaign (i.e. three months post the beginning of the social media campaign).•Change in slope.

In addition to the above model, for both outcomes, we will also fit the following single model (Model 2) that incorporates both the intervention and control series:

$$\text{Model}\;2:\log Y_{t}=\beta_{0}+\beta_{1}t+\beta_{2}I+\beta_{3}\left(t-T_{I}\right)I+\beta_{4}G+\beta_{5}\mathrm{tG}+\beta_{6}\mathrm{IG}+\beta_{7}\left(t-T_{I}\right)\mathrm{IG}+\text{seasonal}+\text{offset}+\epsilon_{t}$$
where

$Y_{t},T_{I},I,t,\text{seasonal},\text{offset and}\;\epsilon_{t}\;$
are as described above.

G
 represents the series with a value of 1 representing the intervention series, and a value of 0 representing the control series.

$\beta_{0}$
,

$\beta_{1}$
,

$\beta_{2}$
 and

$\beta_{3}$
 are as described above for the control series.

$\beta_{4},\beta_{5},\beta_{6}\;\text{and}\;\beta_{7}$
 represent the interactions between time and the intervention series. Specifically,

$\beta_{4}$
 represents the difference in the intercept at the beginning of the series between the intervention and control series,

$\beta_{5}$
 represents the difference in slope between the intervention and control series in the first segment,

$\beta_{6}$
 represents the difference in the level change between the intervention and control series, and

$\beta_{7}$
 represents the difference in the change in slope between the intervention and the control series.

We will compare the estimates of level change at the end of the social media campaign and change in slope between Model 1 and Model 2. This comparison will allow us to assess the possibility of whether a co-intervention/concurrent event may explain our findings.
^
35
^

We will plot interrupted time series graphs for all outcomes and series using the recommendations of Turner et al.
^
43
^ These plots will include: data points, trend lines, seasonality estimation and confidence intervals surrounding the trend line and counterfactual estimates. Segments will clearly delineated by breaks in the trend lines.

Subgroup analysis

We will fit Model 1 for the primary and secondary outcomes for the intervention series separately by:
•Sex (Females, Males)•Location in Perth (North West, North East, Central, South West and South East)

Influencer data

All qualitative information will then be synthesised descriptively, key messages will be identified, with thematic analysis completed using Nvivo software.

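### Cause is to be read from whether a change appears in both series or only one; the between-series contrast in Model 2 is fitted but never named as the estimate that decides

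*Protocol article*

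**What the plan says.** Protocol article, Intervention and control populations: "The control group will be non-Aboriginal young people in the same location". The reason given is that "we expect that any co-interventions or concurrent events would likely affect both groups". Two sentences then say how results will be read. On one side, "if an impact is observed in both groups, this suggests it may be due to a co-intervention/concurrent event"; on the other, "if the impact is only observed in the intervention series, this suggests the effect is more likely to be due to the intervention". The same section commits to recording and reporting other HPV vaccination activity in Perth and whom it targeted.

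Protocol article, Data analysis: Model 1, an uncontrolled segmented model, is fitted separately to each series. The effect measures (level change at campaign end, change in slope) are listed directly after it. Model 2 then joins the two series. Its beta6 is the between-series difference in level change and its beta7 the difference in slope change. The plan will "compare the estimates of level change at the end of the social media campaign and change in slope between Model 1 and Model 2" in order to judge whether a concurrent event could explain the findings. No coefficient is named as decisive and no criterion is given for the comparison.

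For sex and area of Perth: "We will fit Model 1 for the primary and secondary outcomes for the intervention series separately by" these factors. On channels, Stage 2 states that "we will use TikTok as our platform for young people and Instagram and Facebook for families", and it expects followers to create and circulate further content.

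**The concern.** Two separate questions (is there a change here, is there a change there) do not answer whether the changes differ. A large gain in Aboriginal youth beside a small shared gain counts as "both" and is pointed toward a co-intervention, although the difference between the series is what the control was included to show.

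A shared change is not remote. The Introduction reports the 2023 move to one dose, and Data analysis refers to a changed vaccine schedule in the year following the interruption.

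The reading also allows a change in both series only one explanation. With a public social media campaign in the same city, some campaign effect in the control series is a second possible explanation, and the protocol does not mention it.

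At stake is the causal conclusion. A real differential gain could be set aside, or a concurrent event could be credited to the campaign.

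**Working it through.** **1. What comparing the models can show.** In Model 2 the control series' level change is beta2 and the intervention series' is beta2 + beta6. Intercept, trend, level change and slope change all carry an interaction with G. The series-specific changes therefore largely repeat the two Model 1 fits, apart from the shared seasonal and error terms. The new information is beta6 and beta7 with their uncertainty, and the plan does not say that these decide.

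**2. Inputs.** From Sample size: 72 monthly points, AR(1) autocorrelation 0.3, alpha 0.05, a shift of 1 SD, stated power 85%. From Data analysis: the break falls between December 2023 and January 2024. Calendar counting gives 48 + 24 months; the stated 49 + 24 makes 73, so 48/24 is used.

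Assumed, because the document does not give them:
- two-sided testing
- "observed" means p<0.05
- independent series
- ratio k of control SD to intervention SD of 1, 0.5 or 0.3
- a linear model on the SD scale as an approximation to the negative binomial model, without harmonics

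**3. Reproducing the stated power.** Power = Φ(δ/SE − 1.96) + Φ(−δ/SE − 1.96), with SE from generalised least squares. Intercept plus step only: SE = 0.332, power 85.4%. The stated 85% is thus for one uncontrolled series without trend terms.

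**4. Model 1 as specified, one series, δ = 1 SD.**
- Level change at the break: SE = 0.622, power 36%.
- Level change three months later: SE = 0.578, power 41%.

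Ranges below run over these two time points.

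**5. Scenario A: shared change 0.5 SD, true extra 1 SD in the intervention series (1.5 SD in total).** At the break with k = 0.3:
- Intervention: 1.5/0.622 − 1.96 = 0.45, so 0.674.
- Control: SE = 0.3 × 0.622 = 0.187; 0.5/0.187 − 1.96 = 0.72, so 0.764.
- Both: 0.674 × 0.764 = 0.515. Only intervention: 0.674 × 0.236 = 0.159.

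| k | both | only intervention |
|---|---|---|
| 0.3 | 51-61% | 13-16% |
| 0.5 | 24-30% | 43-44% |
| 1 | 9-10% | 59-63% |

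The more precise the control, the more often the reading points away from a real differential effect.

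**6. Scenario B: identical 1 SD change in both series, no true difference.** P(only intervention) = P(intervention) × [1 − P(control)]. With k = 1 at the break: 0.362 × 0.638 = 0.231.

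| k | only intervention |
|---|---|
| 1 | 23-24% |
| 0.5 | 3-4% |
| 0.3 | below 0.1% |

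A two-sided test of the contrast is wrong in 5% at every k.

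**7. Cost of relying on the contrast.** SE(contrast) = SE × √(1 + k²). With k = 1 at the break: 0.622 × 1.414 = 0.880.

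| k | contrast power, 1 SD |
|---|---|
| 1 | 21-23% |
| 0.5 | 30-34% |
| 0.3 | 34-38% |

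**8. Spill-over.** If a share f of the campaign effect reaches controls, the contrast estimates (1 − f) of it. With a 1 SD effect and f = 0.5 it estimates 0.5 SD, with power about 9-13%. With f = 1 it estimates zero.

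**The case against.** The strongest reply is that the plan already contains the controlled analysis. Model 2 is specified for both outcomes, beta6 and beta7 are correctly defined, and the model comparison is meant to address concurrent events. The both/only sentences are hedged, never mention significance and can be read as design rationale. Other local activity will be recorded. Choosing which fitted coefficient is primary is often left to an analysis plan.

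Much of this stands. A reader might infer that attribution rests solely on separate fits; it does not, because Model 2 is planned. What remains is that the only stated rule for reading cause is one of presence or absence, and that nothing in the article makes the contrast override it. That is a matter of what the text fixes, not of missing detail.

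Three further inferences go too far:
- **That controls see the campaign.** This is plausible from the channels and the shared city, but it is not documented. The campaign is targeted at Aboriginal youth and prioritises Aboriginal influencers. The listed analytics include viewer location but not Aboriginal status.
- **That a concurrent event would often pass as a campaign effect.** This needs similarly noisy series. With a precise control the chance is close to zero.
- **That subgroups will be compared by significance.** The plan states separate fits by sex and area but does not say they will be contrasted.

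It is also fair to object that the contrast does not cure spill-over; it subtracts it.

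**Conclusion.** The point holds as one of interpretation and priority among estimates that are already planned. The stated reading can mislead. With a control SD 0.3 of the intervention SD, a true extra 1 SD effect on top of a 0.5 SD shared change shows as "both" in 51-61% of cases. With equal SDs, a purely shared 1 SD change shows in the intervention series alone in 23-24%.

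These figures rest on reading "observed" as p<0.05, on independent series and on assumed SD ratios. The document gives neither the size nor the variability of the control series, so the direction of the problem is firmer than its size. Positive correlation between the series would raise the power of the contrast.

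The contrast is the right quantity for removing shared events. It is not a remedy for spill-over, under which it is biased toward no effect.

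**What to change.** 1. Name the Model 2 contrast at campaign end, beta6 plus beta7 times the months elapsed since T_I, with its 95% CI, as the main attribution estimate, and beta7 as second. The number of months should follow from the break date and campaign end once these are settled.
2. Keep the Model 1 fits as description of each series.
3. Replace the both/only sentences: the effect attributed to the campaign is the between-series contrast. A change in both series is compatible with a concurrent event and also with spill-over, and under spill-over the contrast is biased toward no effect.
4. If effects by sex or area are to be compared, fit one model with subgroup-by-level-change and subgroup-by-slope-change terms and report the interactions with intervals.

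No new data are needed; the cost is wording and precision. For 1 SD in the segmented model, power is about 21-38% for the contrast (k from 1 to 0.3) against 36-41% for a single series. The 85% in Sample size should not be cited for the contrast.
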